## Abstract

**Background:**

Chronic heart failure (CHF) is a public health priority. Its age-standardized prevalence has increased over the past decade. A major challenge for the management of CHF is to promote long-term adherence to self-care behaviors without overtaxing available health care resources. Counseling by multidisciplinary health care teams helps to improve adherence to self-care behaviors and to reduce the rate of death and hospitalization. In the absence of intervention, adherence to self-care is below recommended standards.

**Objective:**

This trial aims to establish and evaluate a Canadian e-platform that will provide a core, standardized protocol of behavioral counseling and education to facilitate long-term adherence to self-care among patients with CHF.

**Methods:**

Canadian e-Platform to Promote Behavioral Self-Management in Chronic Heart Failure (CHF-CePPORT) is a multi-site, double blind, randomized controlled trial with a 2 parallel-group (e-Counseling + Usual Care vs e-Info Control + Usual Care) by 3 assessments (baseline, 4-, and 12-month) design. We will identify subjects with New York Heart Association Class II or III systolic heart failure from collaborating CHF clinics and then recruit them (n=278) by phone. Subjects will be randomized in blocks within each site (Toronto, Montreal, and Vancouver). The primary outcome will be improved quality of life, defined as an increased number of subjects with an improvement of ≥5 points on the summary score of the Kansas City Cardiomyopathy Questionnaire. We will also assess the following secondary outcomes: (1) diet habits, depression, anxiety, smoking history, stress level, and readiness for change using self-report questionnaires, (2) physical activity level, current smoking status, and vagal-heart rate modulation by physiological tests, and (3) exercise capacity, prognostic indicators of cardiovascular functioning, and medication adherence through medical chart review. The primary outcome will be analyzed using generalized estimation equations with repeated measures on an intention-to-treat basis. Secondary outcomes will be analyzed using repeated-measures linear mixed models with a random effects intercept. All significant main effects or interactions in the statistical models will be followed up with post hoc contrasts using a Bonferroni correction with a 2-sided statistical significance criterion of *P*<.05.

**Results:**

This 3.5-year, proof-of-principle trial will establish the e-infrastructure for a pan-Canadian e-platform for CHF that is comprised of a standardized, evidence-based protocol of e-Counseling.

**Conclusions:**

CHF-CePPORT is designed to improve long-term adherence to self-care behaviors and quality of life among patients with CHF. It will demonstrate a distinct Canadian initiative to build capacity for preventive eHealth services for patients with CHF.

**Trial Registration:**

ClinicalTrials.gov NCT01864369; http://clinicaltrials.gov/ct2/show/NCT01864369 (Archived by WebCite at http://www.webcitation.org/6Iiv6so7E).

## Introduction

### Chronic Heart Failure Syndrome

Chronic heart failure (CHF) is a progressive clinical syndrome in which the heart is unable to pump oxygenated blood sufficiently to meet metabolic demands during exercise or at rest [1]. It is a major cause of hospitalization and mortality, and it is the only major cardiovascular disease that is increasing in prevalence [2]. For example, in Canada, the age-standardized prevalence of CHF has risen from 1585 to 2510 cases per 100,000 over the past decade [3]. The 1-year hospital readmission rate is 40% [4], and the mortality rate after the first year of a CHF diagnosis is 25%-40%. Patients with CHF experience many symptoms such as shortness of breath and fatigue [5]. Self-care behaviors are critical to symptom management and quality of life. These behaviors include maintaining a healthy diet that is low in fat and sodium, limiting alcohol and fluid intake, maintaining a healthy body weight, exercising regularly, reducing stress, and smoke-free living [6].

A key challenge is to improve quality of life and long-term adherence to self-care behaviors for patients with CHF without overtaxing health care resources. In the absence of intervention, adherence to self-care is problematic with regard to medications (50%-96%), physical activity (9%-53%), dietary restriction of sodium (20%-71%), and daily monitoring of weight (20%-80%) [7]. Meta-analysis has shown that multidisciplinary counseling to promote self-care following hospital discharge for CHF reduces mortality (relative risk-RR=0.75, 95% CI 0.59-0.96), CHF-related hospitalizations (RR=0.74, 95% CI 0.63-0.87), and all-cause hospitalizations (RR=0.81, 95% CI 0.71-0.92) [8].

### e-Counseling for Patients

We support the conclusions from recent meta-analytic reviews that call for further development of an e-Counseling strategy for patients with cardiovascular conditions, including CHF [8-10]. An e-Counseling strategy may be well suited to reinforce long-term adherence to self-care among patients with CHF, and in turn improve quality of life while reducing the high rate of hospitalization and mortality. The feasibility of this approach is underscored by the observation that 80.3% of Canadians reported having personal access to the Internet in 2010, including 70%-76% in the two lowest income quartiles, 80% who were between 45-64 years old, and 51% between 65-74 years old [11]. Moreover, we surveyed 100 patients with CHF about whether “It was easy for [them] to get access to a computer at home” (1=Strongly disagree, 5=Strongly agree) [12]. The mean response was 4.4, SD=1.1. In keeping with recent studies [13,14], these data indicate that e-Counseling is very likely to be used by patients with CHF in our clinics.

The primary objective of this trial is to establish and evaluate a Canadian e-platform for e-Counseling and education to enhance quality of life and to facilitate long-term adherence to self-care among patients with CHF. This proof-of-principle trial builds upon: (1) previous clinical trials in e-Counseling, telehealth, and telemonitoring, as well as observational studies by our team [12,15-28], and (2) our contributions to Canadian consensus guidelines for the clinical management of CHF [29-31]. This trial will be undertaken in collaboration with the Consumer eHealth platform of the Heart and Stroke Foundation of Canada. Findings from the trial will help extend access to e-Counseling, interactive e-tools, and self-help information for patients with CHF.

## Methods

### Procedures and Features

Procedures and features of our methods have been reviewed according to the Consolidated Standards of Reporting Trials (CONSORT) standards for clinical trials in eHealth [32,33]. It is reported here in accordance with the CONSORT-EHealth (v.1.6.1) checklist [34].

### Trial Design

The Canadian e-Platform to Promote Behavioral Self-Management in Chronic Heart Failure (CHF-CePPORT) is a multi-site, double blind, randomized controlled trial (NCT01864369) with 2 parallel-groups (e-Counseling + Usual Care vs e-Info + Usual Care) and 3 assessment periods (baseline, 4-, and 12-month). Figure 1 shows the research design. This trial was modeled after 2 randomized controlled trials on telehealth and eHealth completed by our team [19,22,23], and after 2 exemplary trials of telehealth that are recently completed [35,36] or in progress [37].

**Figure 1 figure1:**
[figure not shown]
Schematic summary of the trial design.

### Hypotheses

#### Primary Hypothesis

Our primary hypothesis is that more subjects in the e-Counseling + Usual Care arm will experience significant improvement in the quality of life at the 12-month assessment than in the Control arm. This improvement will be defined as a clinically meaningful increase of ≥5 points [38] on the summary score of the Kansas City Cardiomyopathy Questionnaire (KCCQ) [39] from baseline.

#### Secondary Hypotheses

Our secondary hypotheses are that the e-Counseling + Usual Care arm will be associated with significant improvement in the quality of life, adherence to self-care, and psychological adjustment from baseline to 4- and 12-month assessments. These outcomes will be measured using the following objective and validated indices: (1) the KCCQ (≥5 points increase in the summary score at the 4-month assessment) for quality of life, (2) the Canadian version of the Diet History Questionnaire II (DHQ II) [40] for diet habits, (3) the mean 4-day step count (as measured by accelerometry) [41,42] and the Physical Activity Scale for the Elderly (PASE) questionnaire [43] for physical activity level, (4) the medication possession ratio (MPR) [20] for medication adherence, (5) the generalized anxiety disorder (GAD-7) scale [44] and Patient Health Questionnaire (PHQ-9) [45] for anxiety and depressive symptoms, respectively, (6) the Perceived Stress Scale (PSS) [46] for stress level, and (7) Prochaska’s algorithm [47] for readiness to change self-care behaviors.

In addition, we hypothesize that the e-Counseling + usual care group will perform better than the Control groups at the 12-month assessment on the following prognostic measures of cardiovascular functioning: (1) increased exercise capacity as measured by the 6-minute walk test (6MWT) [48], (2) increased vagal-heart rate modulation [44,45] as measured by electrocardiography (ECG), (3) decreased values of the Seattle Heart Failure Model (SHFM) [49-51], N-terminal pro-brain natriuretic peptide (NT-proBNP) [52,53], high sensitivity C-reactive protein (hsCRP) [52,54], and (4) increased VO_2_ peak [55] during cardiopulmonary exercise testing.

### Participant Inclusion/Exclusion Criteria

Patients with CHF will be eligible for the trial if they meet all of the following criteria: (1) male and female patients 18 years or older who are diagnosed with heart failure with reduced ejection fraction (systolic HF) that corresponds to New York Heart Association (NYHA) Class II or III for 3 or more months prior to enrollment, (2) documentation of left ventricular ejection fraction (LVEF) ≤40%, (3) if the patient has been stable throughout 12 months prior to enrollment, documentation will confirm impairment of LVEF by contrast ventriculography, radionuclide ventriculography, or quantitative echocardiography, (4) no worsening of CHF for 1 month prior to recruitment, as determined by the referring cardiologist, (5) confirmation by referring cardiologist that medical treatment includes an optimal and stable dose of angiotensin converting enzyme inhibitor, beta-blocker, and aldosterone antagonist where indicated for at least 1 month prior to enrollment in this study (Patients not treated with a beta-blocker will be enrolled if this was previously prescribed, but not tolerated by them. Use of digitalis or diuretic is optional), (6) subject is not *currently* enrolled in a formal exercise program, (7) comprehension of English or French, (8) subject is familiar with the use of and has access to a personal computer, email, and the Internet, and (9) subject provides informed written consent.

Patients with CHF will be ineligible if they fit with any of the following exclusion criteria: (1) documentation at enrollment of renal failure (serum-creatinine ≥300 micromoles/L, ≥3.0 mg/dL), significant liver disease (alanine transaminase >3-fold upper limit of normal), or poorly controlled diabetes mellitus (fasting blood glucose >10 mmol/L or hemoglobin A1c >8%, or current diagnosis of autonomic neuropathy, ketoacidosis, or hyperosmolar state), (2) current symptomatic hypotension and/or systolic blood pressure ≤85 mmHg, (3) persistent systolic or diastolic hypertension (systolic >170 mmHg or diastolic >100 mmHg despite antihypertensive therapy), (4) CHF secondary to any of the following conditions–primary uncorrected valvular cardiomyopathy, predominant right-sided heart failure, or noncardiac disease (eg, pericardial disease, complex congenital heart disease), (5) cardiovascular comorbidities/procedures that include stroke, acute myocardial infarction, or planned cardiac surgery within 4 weeks before enrollment, (6) severe obstructive, restrictive, or other chronic pulmonary disease, (7) previous heart transplant or is on a wait list for heart transplant at the time of enrollment, (8) diagnosis of major psychiatric disorder (eg, psychosis) or drug/alcohol abuse in past year, and (9) diagnosis of noncardiac disease (eg, cancer) that is likely to shorten life expectancy to <2 years.

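### The renal-failure exclusion prints two creatinine limits that are not the same value, so creatinine of about 265 to 299 micromol/L is excluded by one and not by the other

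*Protocol article*

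**What the plan says.** The eligibility section of the protocol article lists nine exclusions and makes each of them sufficient on its own: "Patients with CHF will be ineligible if they fit with any of the following exclusion criteria". The first begins with "documentation at enrollment of renal failure", and defines it in parentheses as "serum-creatinine ≥300 micromoles/L, ≥3.0 mg/dL".

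Only a comma joins the two values. The article gives no conversion factor, does not say which unit governs, and states no other creatinine limit.

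**The concern.** A limit followed directly by a second limit for the same analyte in another unit reads as one threshold restated. Here the restatement is not numerically true, so the criterion has two cut-offs. Between them, two screeners can each follow the printed text and reach opposite decisions about the same patient.

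This is a hard entry rule. Under Recruitment Procedure, coinvestigator cardiologists identify eligible patients, and the trial recruits from three hospitals. If different units were used in practice, the enrolled population could differ between sites. Even with one unit throughout, an enrolment inside the band could be called compliant or a protocol deviation, according to which figure a monitor applied.

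**Working it through.** **Inputs**

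- Limit in SI units: 300 micromol/L (exclusion criterion 1).
- Limit in conventional units: 3.0 mg/dL (same criterion).
- Molar mass of creatinine, C4H7N3O. This is not in the article and is an assumption from atomic weights: 4 × 12.011 + 7 × 1.008 + 3 × 14.007 + 15.999 = 113.12 g/mol.

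**Can the printed pair be reproduced?** For 3.0 mg/dL to equal 300 micromol/L, the factor would have to be 300 / 3.0 = 100 micromol/L per mg/dL. That corresponds to a molar mass of 10 000 / 100 = 100 g/mol, which is not creatinine's. The pair does not reproduce.

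**Conversion.** 1 mg/dL = 10 000 micrograms/L, so 1 mg/dL = 10 000 / 113.12 = 88.40 micromol/L.

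- 3.0 mg/dL × 88.40 = 265.2 micromol/L
- 300 micromol/L / 88.40 = 3.39 mg/dL
- Gap: 300 − 265.2 = 34.8 micromol/L, or 3.39 − 3.00 = 0.39 mg/dL
- Relative gap: 34.8 / 265.2 = 13.1% of the lower limit; 34.8 / 300 = 11.6% of the higher

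**Sensitivity to the factor and to rounding**

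| Variant | 3.0 mg/dL in micromol/L |
|---|---|
| Factor 88 | 264 |
| Factor 88.4 | 265.2 |
| Factor 88.5 | 265.5 |
| Factor 90 | 270 |
| 3.0 taken as rounded from 2.95 to 3.05 (factor 88.40) | 260.8 to 269.6 |

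None comes near 300. The two would agree only if rounded to a single significant figure (265 to the nearest 100 is 300). That may explain how the pair arose, but it does not make the two cut-offs equal when they are applied.

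**Decision on this criterion at selected values**

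| Creatinine, micromol/L | mg/dL | Excluded by 300 micromol/L | Excluded by 3.0 mg/dL |
|---|---|---|---|
| 264 | 2.99 | no | no |
| 266 | 3.01 | no | yes |
| 280 | 3.17 | no | yes |
| 299 | 3.38 | no | yes |
| 300 | 3.39 | yes | yes |

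The disagreement runs in one direction only: the mg/dL figure excludes patients whom the micromol/L figure does not.

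**Does the comma settle it?** Read as *or*, the lower limit (3.0 mg/dL) governs and 300 micromol/L does nothing. Read as *and*, 300 micromol/L governs and 3.0 mg/dL does nothing. Read as a restatement, one of the two is wrong. On every reading at least one printed figure is wrong or redundant. The same criterion writes an explicit *or* between its glucose and hemoglobin A1c limits, so where alternatives are meant the authors say so.

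**The case against.** The arithmetic is not in dispute; the case on the other side concerns consequence.

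- **Site differences are not shown.** All three hospitals are in one country, the criterion gives the SI value first, and its glucose limit appears only in mmol/L. This suggests that SI units are the working system and the mg/dL value a loose equivalent. If every site screens in one unit, the rule is applied uniformly. This stands as a reason to treat site differences as possible rather than likely. It does not remove the inconsistency, because the article never says that the SI figure governs.
- **A determinate reading exists.** Since any exclusion suffices, the comma can be taken as *or*, and the lower limit then decides. The reading is possible, but the text does not confirm it, and it conflicts with the inference that the SI figure is the working one. Two reasonable readers would therefore apply different limits.
- **The treatment comparison is protected.** Eligibility is settled before randomization, assignment is in permuted blocks balanced across sites, and neither the primary outcome nor the models use creatinine. This stands in full.
- **The number affected is unknown.** This also stands: the article gives no creatinine distribution, so no count among the planned 278 can be derived. Patients in the band must still meet every other criterion, so the micromol/L figure leaves them *not excluded on this point*, not eligible outright.

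**Conclusion.** The concern holds. The two printed limits differ by about 35 micromol/L (0.39 mg/dL; 11.6% to 13.1%), and they give opposite answers on this criterion for creatinine from about 265 to just under 300 micromol/L (3.00 to just under 3.39 mg/dL). The only outside input is creatinine's molar mass, and the conclusion does not depend on how the conversion factor is rounded.

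The consequence is confined to eligibility and the classification of deviations. There is no effect on sample size, type I error or the planned analysis, and no bias between arms is shown. It is still worth correcting, because it is a decision threshold in a mandatory entry rule and nothing else in the article resolves it.

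**What to change.** Reconcile the two figures in exclusion criterion (1): state one limit in one governing unit and, if a second unit is kept, give the correct conversion of that same limit. The clinical investigators must say which limit was intended; this review takes no position on that. Carry the corrected wording into any screening document built from the criterion.

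The cost is a one-line change to the eligibility text. Recruitment Procedure reports that ethics approval was still being sought for Vancouver and Montreal at submission of the article, so at that stage the correction could have gone in before those sites opened. If recruitment has already begun, enrolments and exclusions with creatinine in the affected band should be identified, and the limit actually applied to each recorded.

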### Recruitment Procedure

Cardiologists, who are coinvestigators in this trial, will identify patients with CHF in their care who meet our recruitment criteria. A clinic staff member will introduce the study to the potential subjects and solicit their verbal consent to be contacted by our research team. The contact information of consented individuals will be sent via secure fax to the Behavioral Cardiology Research Unit at University Health Network (UHN), Toronto, Canada. Individuals will be telephoned by our research team to obtain verbal consent to participate and to schedule a baseline assessment appointment to be held at one of the three trial sites (Toronto, Montreal, and Vancouver). We will obtain written informed consent from subjects for trial participation, email communication, and review of medication history at the beginning of their baseline assessment appointment. Once they have completed their baseline assessment, subjects will be randomized into the intervention or control group. We have received ethics approval from our coordination site (UHN). At the time of manuscript submission, we are seeking ethics approval from the Vancouver and Montreal trial sites.

### Intervention

#### Clinical/Theoretical Framework

New taxonomies of techniques for health behavior change have been reported [56,57]. Based on this work, our team has recently published a systematic review of how behavior change techniques are utilized in trials of e-Counseling [58]. Our key finding is that e-Counseling programs that were efficacious used a repertoire of at least six behavior change techniques that can be tailored to (or selected by) the individual user. Further, it is critical to present these techniques in an organized manner, within a framework of preventive counseling that is evidence-based and clinically relevant.

CHF-CePPORT is not “therapy” per se. However, our e-Counseling protocol incorporates key components of two foundational models of behavioral counseling: (1) motivational interviewing (MI) [59], and (2) cognitive-behavioral therapy [60-62]. MI was developed as a set of procedures [63] that build upon educational strategies used in Prochaska’s transtheoretical model [47,64]. The initial goal of MI is to validate the patient’s presenting stage of “readiness” and to tailor feedback or information accordingly. Therapeutic interactions and self-assessment procedures are designed to evoke positive “change talk,” [63] as the patient is directed to identify personally salient goals that are associated with potential change in a targeted behavior. As ambivalence about change is resolved, the patient is directed to “experiment” with behavior change. Goals for change and behavioral feedback are conventionally provided in a manner that is consistent with cognitive-behavioral therapy [60-62]. Strategies to sustain change are collaboratively reviewed to assist the patient in: (1) developing a repertoire of behavioral skills, and (2) building efficacy from performance-based feedback. Meta-analysis shows that in comparison to a standardized intervention or usual care, MI (alone or combined with cognitive-behavioral counseling) is associated with significantly greater reduction in body mass index, total cholesterol, blood pressure, adult smoking, and alcohol abuse, and with increased adherence to diet, exercise, and other “treatment” [65-67].

#### Intervention (e-Counseling + Usual Care) Group

The e-Counseling protocol in CHF-CePPORT builds upon evidence and know-how that we have shown in our previous trials. In the Community Outreach Heart Health and Risk Reduction Trial (COHRT) [23,68,69], we demonstrated that an evidence-based model of telehealth counseling with MI [59] added therapeutic benefit to a recommended standard of preventive counseling at a 6-month follow-up in people with or at elevated risk for cardiovascular disease. In the Internet-Based Strategic Transdisciplinary Approach to Risk Reduction and Treatment (I-START) [19,22,28], our e-Counseling protocol was independently associated with reduced systolic blood pressure, pulse pressure, and total cholesterol (but not with diastolic blood pressure), as well as with increased adherence to psychometrically assessed exercise and diet in people with hypertension. Through our ongoing trial, e-Counseling Promotes Blood Pressure Reduction and Therapeutic Lifestyle Change in Hypertension (REACH) [21], we are establishing whether our e-Counseling protocol independently reduces blood pressure and 10-year absolute risk for cardiovascular disease over a 12-month interval in people with hypertension. The CHF-CePPORT e-Counseling protocol builds upon this evidence [19,22,23,68,69], as well as guidelines from notable trials and reviews of telehealth and eHealth [14,35,37,70-72]. This trial will be a proof-of-principle study for patients with CHF.

The CHF-CePPORT e-Counseling protocol will be delivered in collaboration with the Consumer eHealth platform of the Heart and Stroke Foundation of Canada. It will send 28 emails proactively to each subject in the intervention arm over a 12-month interval (Table 1). Each email will link e-Counseling subjects to a restricted section of our e-platform where they will access multimedia materials and interactive e-tools. As noted above, the clinical method and content of this protocol is consistent with principles of MI. In keeping with I-START [19,22], the e-Counseling messages promote the following: (1) explicit validation of the subject’s stage of “readiness” for behavior change via e-messaging and educational segments, (2) collaborative participation by means of subject-selected menus and explicit messaging to validate the subject’s active participation, and (3) reinforcement of “change talk” [63] through peer modeling, dramatic vignettes, and self-help exercises that are designed to help resolve ambivalence to change. Additionally, MI is most efficacious when combined with other evidence-based counseling methods such as cognitive-behavioral therapy [66]. Accordingly, the e-Counseling protocol will maintain a user-centered approach by working collaboratively with each subject who reports appropriate motivation to change a behavior that they have identified as a priority for change. This includes interactive access to the following therapeutic tools: (1) self-help information and e-tools for self-monitoring self-care behaviors, and (2) developing cognitive-behavioral skills to build and strengthen efficacy [73] to initiate and maintain behavior change. The collaborative tone of the e-Counseling content is consistent with cognitive-behavioral guidelines to reinforce motivation [59,63] and efficacy [73]. Finally, subject engagement in this segment of the e-Counseling program will be reinforced through the use of short films that will complement the e-based self-help information and e-tools. These original short films have been written and produced by our research team, in collaboration with the Heart and Stroke Foundation of Ontario. e-Counseling subjects will continue to receive CHF-related medical care from their health care team during the course of the trial (ie, usual care).

**Table 1 table1:** The 12-month schedule for proactive e-messaging for the CHF-CePPORT trial.

	Month 1-4	Month 5-8	Month 9-12
Schedule for proactive e-messages	Weekly	Biweekly	Monthly
Total # of proactive e-messages	16	8	4

